### Sample size and data analytic approach

Simulation work has shown that large sample sizes are required to develop accurate predictive models of treatment response [102, 103]. Our own statistical simulation shows that given the two-site, split-half validation design, we require 300 participants per site—at least 300 to develop the model and another 300 to adequately validate it in this Stage 1 model. The reality is that underpowered studies likely detect only the largest effects, and multivariate models based on them yield unstable predictions that overfit the sample data and perform poorly out-of-sample [104, 105]. As pointed out by Kessler and colleagues, “The inevitable conclusion is that samples much larger than those in existing mental disorder randomized clinical trials are required to develop useful personalized treatment recommendations” [106]. The overarching message of the statistical learning literature and our own simulations used to develop this proposal is “go big or go home”.

Our primary objective is to build a model predicting EBT non-response using a multivariate combination of candidate predictors. One set of predictors constitutes what we consider our “control” model; these include “traditional” prognostic factors and psychological variables (see Table 1). The addition of a second set of predictors, corresponding to our proposed measures of reactivity to CO_2_ and VH, constitutes our “experimental” model. We have two key hypotheses that we aim to test: (1) the experimental model will outperform the control model when predicting never-before-seen data, establishing the additive predictive value of assessing reactivity measures prior to initiating treatment; and (2) when predicting never-before-seen data, a model that excludes VH reactivity measures will outperform a model that excludes CO_2_ reactivity measures, establishing that the additive predictive value is specific to CO_2_ reactivity.

**Table 1 Tab1:** Schedule of assessments

Measurement Domain	Screen	Biomarker Visit	Treatment (Weeks 1–12)	Follow-up (Weeks 13, 24)

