Hypothesis testing will be based on a series of model comparisons. All models will be fit to the train site and used to predict the probability of treatment response at the test site. These probabilities will be used to generate an ROC curve for each model’s ability to discriminate treatment responders from non-responders. Significant differences between curves will be evaluated using DeLong’s test for two correlated ROC curves as implemented by the R package “pROC”. The following model comparisons will be performed:All candidate predictors vs. excluding CO_2_/VH reactivity measures. This comparison addresses the question: do the novel measures of CO_2_/VH reactivity add predictive value beyond traditional—and easier to collect—measures like diagnosis or symptom severity? We hypothesize that the addition of the reactivity measures will significantly improve model performance. If CO_2_ reactivity is completely confounded with these competing predictors, then adding it to the model will not result in any predictive gains; CO_2_ reactivity can only improve model predictions if it provides unique information that is not captured by “confounders”.CO_2_ vs. VH reactivity. Finally, if the above model demonstrates the value of collecting CO_2_ reactivity measures, we will next assess does CO_2_ reactivity specifically predict treatment non-response (by revealing something about the underlying biology), or is it merely heightened sensitivity to the physiological sensations that are common to both CO_2_ inhalation and hyperventilation? Qualitatively, if VH reactivity has no predictive utility, then the statistical learning algorithm will have penalized these measures out of the model entirely by this point. However, the hypothesis of mechanistic specificity will be more formally tested by comparing a model that includes just CO_2_ reactivity measures to one that includes just VH reactivity measures. Note that the ability to perform a head-to-head comparison like this is one of the advantages of comparing ROC curves in an independent test set; the models do not need to be nested as they would when performing likelihood ratio tests on model fits.

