Two strengths of this validation strategy should be emphasized. First, the significance of the biomarkers will be determined by their ability to outperform self-report measures, not just that their coefficients are significantly different from zero. The former speaks to their real-world utility; the latter does not. Second, the biomarkers are being compared on their ability to predict new data, not just their ability to fit the same data. This design/analytic feature helps ensure that we do not propagate failure-to-replicate issues. If we do not replicate a simplified model across sites and our hypotheses are not supported by the data (and there is not support for an alternative model with adequate sensitivity and specificity), we will recommend to the field that reactivity to CO_2_ and/or VH challenge (and the confounder variables we assessed) should not be used for determining patients’ suitability for EBT. Our use of a replicated assessment and a large sample helps instill confidence in these recommendations.

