#### Statistical power

We ran 5,000 computer simulations of our study design under a wide range of total sample sizes. In brief, a different multivariate distribution was defined for each of the following five diagnostic categories: (1) PD(with or without agoraphobia), (2) SAD, (3) GAD, (4) OCD, and (5) PTSD. Data were simulated to match the disorder-specific response rates (PD = 0.53, SAD = 0.45, GAD = 0.47, OCD = 0.43, PTSD = 0.59) reported in a meta-analysis of 87 studies [135]. The specified *N* for a given simulation was divided equally across the 2 sites and 5 disorder groupings within sites, and random samples of size *N*/10 were drawn for each disorder group for each site, one of which was arbitrarily labeled “train” and the other “test”. Just as we specified in our analytic plan, elastic-net logistic regression models were fit to the train site, and the optimal penalty mix (parameter alpha) and magnitude (parameter lambda) were selected using the average of 10 repeats of a tenfold cross-validation procedure. We then used this model to predict the response at the test site. These predictions (which are individual probabilities of response) and the actual response values were then used to generate ROC curves for the different models to be compared. The control model, which includes only “traditional” self-report measures, was assumed to have a true AUC of 0.63, and the experimental model, which adds CO_2_ and hyperventilation reactivity measures, was simulated to have a true AUC of 0.73. These values and their differences correspond to our minimal effect size of interest.

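### The rule for recommending against CO2/VH reactivity and the confounder variables never asks that a gain of 0.10 AUC be excluded, and neither listed model comparison evaluates the control model

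*Protocol article*

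**What the plan says.** The rule is in the protocol article, Model development and validation strategy. Its first two conditions are: "If we do not replicate a simplified model across sites and our hypotheses are not supported by the data". A parenthesis adds a third: "and there is not support for an alternative model with adequate sensitivity and specificity". If all three hold, "we will recommend to the field that reactivity to CO_2_ and/or VH challenge (and the confounder variables we assessed) should not be used" to decide whether a patient is suitable for exposure-based therapy. The same paragraph says that replication and the large sample lend confidence to this advice.

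The same section lists two comparisons, both DeLong tests of two ROC curves at the test site:

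- Comparison 1: "All candidate predictors vs. excluding CO_2_/VH reactivity measures".
- Comparison 2, run only if the first shows value: "comparing a model that includes just CO_2_ reactivity measures to one that includes just VH reactivity measures".

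The control model is described under Sample size and data analytic approach: "these include “traditional” prognostic factors and psychological variables (see Table 1"). It is therefore the reference in comparison 1.

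Under Statistical power, the control model, made up of traditional "self-report measures, was assumed to have a true AUC of 0.63", and the experimental model was simulated at 0.73. The article adds: "These values and their differences correspond to our minimal effect size of interest". The tests there are directional at p < 0.05, with 92.2% power for comparison 1 at 300 training and 300 test participants.

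**The concern.** A superiority test that misses p < 0.05 may mean that the gain is too small to matter, or that the data cannot tell. The plan names the gain that matters (0.10 AUC) but does not use it when it draws the negative conclusion. An inconclusive result and a truly negative one can therefore meet the hypothesis condition in the same way, although the advice to the field should differ.

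The reach of the advice is a second problem. The confounder variables are in both models of comparison 1, and comparison 2 sets CO2 against VH. A failed comparison 1 is a statement about what reactivity adds. It carries no verdict on the control model, and it becomes more likely the better the control model predicts. What is at stake is public advice that a marker, and a set of questionnaires, should not be used.

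**Working it through.** **Inputs** (Statistical power): AUC 0.63 and 0.73, so a gain of 0.10; one-sided alpha 0.05 (z = 1.645); power 92.2% (z = 1.419); 300 test participants. The mean response rate is (0.53 + 0.45 + 0.47 + 0.43 + 0.59)/5 = 0.494, or about 148 responders and 152 non-responders.

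**The plan's power figure.** A binormal simulation with DeLong's test, 152/148 patients and one-sided 0.05 gives 91% power if the two model scores correlate at 0.4 and 93% at 0.5. The article does not give this correlation, so 92.2% is plausible but not strictly reproducible. The steps below take it as stated.

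**One direction, complete data**

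- Implied standard error of the gain: 0.10/(1.645 + 1.419) = 0.0326.
- Non-significant if the observed gain is below 1.645 × 0.0326 = 0.054.
- Highest upper one-sided 95% limit of a non-significant result: 2 × 1.645 × 0.0326 = 0.107.
- At a true gain of 0.10: non-significant in 1 − 0.922 = 7.8% of tests; upper limit below 0.10 in 5.0%.
- Non-significant but 0.10 not excluded: 7.8% − 5.0% = 2.8%.

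**Both directions, treated as independent (an assumption)**

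- At least one fails at a true gain of 0.10: 1 − 0.922² = 15.0%. Both fail: 0.078² = 0.6%.
- Standard error of the mean gain: 0.0326/√2 = 0.0231. The pooled limit is the mean gain + 1.645 × 0.0231 = mean gain + 0.038, so it includes 0.10 when the mean gain exceeds 0.062.
- If both fail, the mean gain is below 0.054 and the pooled limit below 0.054 + 0.038 = 0.092. It always excludes 0.10, so the gap vanishes.
- The pooled limit falls below 0.10 in 5.0% of all trials at the planned gain. At least 15.0% − 5.0% = 10.0% of trials therefore have a failed direction and a pooled limit that still includes 0.10. Numerical evaluation gives 10.4%. All of these are trials in which exactly one direction failed.

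**Missing outcomes (20% loss assumed, test-site effect only)**

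- Standard error: 0.0326/√0.8 = 0.0365. Threshold: 1.645 × 0.0365 = 0.060. Highest limit of a non-significant result: 0.120.
- Non-significant at a true gain of 0.10: Φ((0.060 − 0.10)/0.0365) = 13.7%.
- Non-significant without excluding 0.10: 13.7% − 5.0% = 8.7%, about 9%.

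**Is a negative conclusion still reachable under an interval rule?** At a true gain of zero, one direction excludes 0.10 with probability Φ(0.10/0.0326 − 1.645) = 92%. The binormal simulation gives 84% to 96% for score correlations of 0.3 to 0.6.

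**The case against.** The strongest reply is that the rule is harder to trigger than it looks. Its three conditions are joined by *and*. A reader might infer that unsupported hypotheses alone lead to the negative advice; the text does not say so. A control model that predicted well enough could block the advice through the alternative-model clause. This stands, and it limits how often the gap could matter. It does not supply a margin for the gain, and the article puts no figure on adequate sensitivity and specificity.

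A reader might also infer that nothing planned could ever test the questionnaires. That goes too far. Each model gets a test-site ROC curve, and Deriving treatment recommendation heuristics compares decision rules built from easy-to-obtain measures with a no-information model. Those measures are not listed and may include questionnaires. The Discussion also promises an account of the best-predicting model if the hypotheses fail. What remains is that neither listed model comparison evaluates the control model itself.

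Two further figures are tempting but do not bear on the trigger. The 82.7% power for CO2 against VH concerns a test run only after comparison 1 has succeeded. And a control AUC of 0.63 may be clearly above 0.5 without being fit for selecting treatment, which is the standard the advice invokes: in the article's worked example the baseline model finds 4 true non-responders among 5000 patients at the 80% cutoff.

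Finally, a condensed article may leave interval reporting and thresholds to a fuller document. That is fair for reporting detail. The rule for the public conclusion, however, is stated in the article itself and rests on hypotheses being unsupported.

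**Conclusion.** The point holds in a limited form. The negative recommendation depends in part on failed superiority tests, without a requirement to exclude the plan's own minimal effect of 0.10, and the listed comparisons cannot carry a verdict on the confounder variables.

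For CO2/VH the size is modest. With complete data the gap is 2.8% of single tests at the planned gain, and none when both directions fail and are pooled. It is mainly a matter of disagreement between sites: about 10% of trials with a true gain of 0.10 would move from a possible negative recommendation to inconclusive. At an assumed 20% loss of outcomes the single-test figure rises to about 9%.

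These figures rest on the stated 92.2% power, a normal approximation and independent directions. They describe the comparison 1 part of the rule and are not the probability that all three conditions are met. The 10% also assumes that a split between sites counts as non-support, which the article does not settle. The power calculation and the planned tests are not in question.

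**What to change.** Change the conclusion rule in two places.

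1. Issue the negative recommendation on CO2/VH reactivity only if the upper one-sided 95% limit of the AUC gain in comparison 1 is below 0.10; otherwise report the result as inconclusive. Use either each direction's DeLong limit or one combined limit. A combined limit should come from a resampling method that respects the reuse of both data sets with roles swapped, because the article plans no pooled estimate.
2. Take the confounder variables out of that recommendation, or base it on the control model's own test-site AUC, sensitivity and specificity with confidence limits, judged against a stated level of adequacy.

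The cost is a few sentences and a little extra analysis. Per-direction limits follow from the DeLong analyses already planned; a combined limit needs some programming. No new data are needed. The downside is that some results now read as negative would be reported as inconclusive.

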#### Translating anticipated ROC gains into clinical impact

The comparison of the ROC model curves is a framework for hypothesis testing, but the model will ultimately need to be couched in other terms besides an improvement in the ROC to convince clinicians of its practical utility, which depends not only on the improved performance of the model, but also clinical judgment about the optimal tradeoff between sensitivity and specificity: one can always boost the gain in the correct number of non-responders at the cost of increasing the number of falsely identified non-responders, and individual clinicians and patient circumstances may dictate different cut points. Thus, a metric like ROC that captures the overall tradeoff between specificity and sensitivity across all possible decision thresholds is the best way to frame our minimal objective, keeping in mind that this is a conservative expectation; larger predictive gains are possible.

However, assuming the minimal gains in ROC performance that we used to determine sample size requirements, we can offer a working example for one potential cutoff: if we were to require greater than an 80% predicted probability of non-response to forego a trial of EBT, then, out of 5000 patients entering treatment, the standard baseline model would only identify 4 true non-responders and falsely identify 1 responder as a likely non-responder. In contrast, the addition of CO_2_ reactivity measures would identify 262 true non-responders while misidentifying 26 responders as non-responders. This would spare > 10% of non-responders from an unsuccessful trial of EBT vs. < 0.2% under the baseline model, while incorrectly excluding only 1% of would-be responders. The biomarker assessment burden in our protocol is a single session, balanced against 12 one-hour sessions of treatment. The ability to spare 1/10 non-responding patients from the burden of unsuccessful treatment, while only negatively impacting 1/100 responding patients, justifies the burden of a single assessment session, in our opinion.

#### Deriving treatment recommendation heuristics

The final data product is to translate the above models into algorithmic recommendations to determine whether a patient is very unlikely (*e.g.,* < 30% chance) to respond to EBT, which could support the recommendation of interventions that do not rely on fear extinction (e.g., other psychosocial interventions, pharmacological interventions). Although we chose a statistical learning algorithm that avoids “black box” predictions, obtaining a probability of non-response will still require inputting a number of measurements into something like a web-based calculator, which we will disseminate if the models demonstrate good predictive value. But clinicians might be more likely to adopt a treatment recommendation for a patient if they are able to derive it from decision rules (e.g., if a patient maintains a latency less than 90-s between CO_2_ inhalations) based on the measurements that are easiest to acquire. We will attempt to derive such decision rules by applying a recursive partitioning algorithm to the data (similar to the approach used to assist hospital pharmacy staff in identifying patients at risk of medication errors)[134] using only easy-to-obtain measures. We will then use the same model comparison strategy outlined above to compare the predictive performance of the decision rules to both a no-information model and the best models derived from elastic-net regression. If the simplified heuristic model offers significant gains over no information and is not significantly worse than the best models, then this will provide the ideal mechanism for translating the knowledge gained from this study to clinical practice.

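### A calculator of individual non-response probability may be released, but the only test-site evaluation stated for the models behind it is ROC comparison, which cannot show whether a displayed probability is right (minor)

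*Protocol article*

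**What the plan says.** **The product.** In the protocol article, Deriving treatment recommendation heuristics, the end product is a set of recommendations to "determine whether a patient is very unlikely (*e.g.,* < 30% chance) to respond to EBT". The article adds that an individual non-response probability would come from an online tool into which the clinician enters the measurements. Its release is conditional: "which we will disseminate if the models demonstrate good predictive value". That condition carries no metric or threshold. A simpler set of decision rules is also planned.

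**The evaluation.** Under Model development and validation strategy, each site's models predict the other site's patients, and "These probabilities will be used to generate an ROC curve" for each model. Curves are compared by DeLong's test. Statistical power describes the same sequence: "elastic-net logistic regression models were fit to the train site", test-site probabilities, ROC curves, DeLong's test. The simplified rules are to be assessed by the same comparison strategy.

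**What else is said.** Translating anticipated ROC gains into clinical impact gives ROC the role of hypothesis testing and says "the model will ultimately need to be couched in other terms besides an improvement in the ROC". It then offers a worked example from the planning assumptions: "if we were to require greater than an 80% predicted probability of non-response to forego a trial of EBT". Model development and validation strategy also mentions adequate sensitivity and specificity, in the sentence on what happens if the hypotheses fail, without a cut-off or value. The tenfold cross-validation tunes the penalty within the train site and is not a check at the other site.

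**The concern.** A calculator that shows a probability, and a recommendation triggered when that probability passes a cut-off, both depend on the number being right in absolute terms. An ROC curve depends only on how patients are ordered. Shift every predicted logit by a constant, or stretch it, and the curve, the AUC and DeLong's statistic do not move, while the patients crossing a fixed cut-off do.

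The stated evaluation therefore does not test what the calculator outputs. Two things could make the displayed probability wrong at a new site: chance variation in a penalised model fitted to 300 patients, and a real difference between sites in response rate or case mix. At stake is how far a displayed risk can be trusted when it is used to support steering a patient away from a first-line treatment.

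**Working it through.** **1. The plan's own figures.** Mean response is (0.53 + 0.45 + 0.47 + 0.43 + 0.59)/5 = 0.494, so non-response is 0.506. Of 5000 patients, 2530 are non-responders and 2470 responders. The worked example at the 80% cut-off then gives 262/2530 = 10.4%, 4/2530 = 0.16% and 26/2470 = 1.05%. These match the stated more than 10%, less than 0.2% and 1%.

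**2. ROC comparison ignores calibration.** In one simulated test set of 300, the two AUCs were 0.6000 and 0.7114 with DeLong z = 3.6249. Shifting the second model's logits by +1 or -1, or doubling them, left all three values unchanged.

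**3. What a shift does at a cut-off, with AUC fixed.** Assume equal-variance normal scores with AUC 0.73, so d = √2 × Φ⁻¹(0.73) = 0.867. If predicted logits are too high by s, the score threshold for a displayed probability t is

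c = [logit(t) − logit(0.506) − s + d²/2] / d.

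Responders flagged = 1 − Φ(c); non-responders flagged = 1 − Φ(c − d); true risk at the cut-off = expit(logit(t) − s). For t = 70%, c = (0.847 − 0.024 − s + 0.376)/0.867:

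| s (assumed) | c | responders flagged | non-responders flagged | PPV | true risk at a displayed 70% |
|---|---|---|---|---|---|
| −0.25 | 1.672 | 4.7% | 21.0% | 82% | 75% |
| 0 | 1.383 | 8.3% | 30.3% | 79% | 70% |
| +0.25 | 1.095 | 13.7% | 41.0% | 75% | 64.5% |

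The shifts are assumptions; the article gives no figure for them. This simple model does not reproduce the article's raw counts (at 80% it gives 322 and 55, against 262 and 26). The article's simulation distributions are not given, so that is not an error.

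**4. Variation between fits at identical sites.** Assumptions: 14 control predictors (5 active), 4 CO₂ and 4 VH predictors; correlation 0.25 within block and 0.14 between CO₂ and VH; true AUC 0.733; elastic-net logistic regression on 300 patients with 2 repeats of tenfold cross-validation (the plan uses 10). Each of 400 fits was evaluated on 40,000 patients from the same population.

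| quantity | centre | central 95% of fits |
|---|---|---|
| AUC | mean 0.708 | 0.683 to 0.723 |
| calibration slope | median 1.085 | 0.736 to 1.862 |
| calibration intercept | SD 0.124 | −0.237 to +0.241 |
| true non-response at predicted 67.5–72.5% | mean 72.1% | 63.3% to 83.9% |
| responders flagged at 70% | mean 6.1% | 0.3% to 13.8% |
| non-responders flagged at 70% | mean 21.1% | 2.9% to 37.8% |

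The correlation between AUC and responders flagged was −0.05. Among the 182 fits with AUC 0.69 to 0.71, responders flagged still ran from 1.1% to 14.4%. With 16 or 32 assumed predictors (200 fits each) the ranges were 1.1% to 12.1% and 0.8% to 13.6%. A separate run of 91 fits under the same predictor assumptions gave slope 0.76 to 1.70, intercept −0.21 to +0.26, responders flagged 1.0% to 13.3%, and PPV of patients flagged at 70% of about 73% to 87%.

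**5. What 300 test patients can show.** The estimated intercept has total SD 0.174 across simulated studies, of which 0.124 is real variation between fits. The sampling SE is √(0.174² − 0.124²) = 0.122. A 5% test would reject beyond 1.96 × 0.122 = 0.239. That flags about 17% of fits, since 0.239/0.174 = 1.37 SD, and it detects a true error of 0.24 about half the time.

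**The case against.** Much of the opposing case stands.

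- **ROC is right for its stated job.** The article uses it for hypothesis testing, and rank comparison suits both hypotheses.
- **The release condition is open.** An analysis plan that is not shown could define it to include calibration. A reader might infer that AUC alone decides release; the article does not say so, and it states that terms other than ROC will be needed. The point survives only because the article itself describes both the product and the validation, and the validation described does not examine what the product displays.
- **The harm is gated.** This is a Stage 1 study. The Discussion makes moving patients to other treatments conditional on specificity to EBT, which is left to later work, and the 30% figure is only an example. However, release of the calculator is not itself made to wait for that work.
- **The simulated harm is small.** A reader might take responders flagged of 0.3% to 13.8% as the size of the miscalibration. It is not, because that figure also reflects how widely a fit spreads its predictions. Even combining the two upper limits, which need not come from one fit, PPV is 0.506 × 0.378 / (0.506 × 0.378 + 0.494 × 0.138) = 0.191/0.259 = 74%. The typical slope is above 1, so high displayed risks are usually conservative.
- **A pass/fail calibration test would be weak**, as step 5 of the working shows.

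A reader might also see the 70% and 80% non-response cut-offs as a contradiction. Both are offered as illustrations, so they are not.

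**Conclusion.** The point holds as a minor one. The stated test-site evaluation cannot show whether the calculator's probabilities, or recommendations at a probability cut-off, are right at another site. The remarks on sensitivity, specificity and terms beyond ROC do not supply that check.

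A reader might infer that the calculator would be seriously wrong or would exclude many responders by mistake. The documents do not support this. With identical sites, expected miscalibration is modest and flagged patients generally have more than 70% non-response. What remains is that a single released fit may be off (about 63% to 84% true non-response at a displayed 70%) with nothing in its AUC to reveal it, and that a real site difference of unknown size could add to this.

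The rank-only property needs no assumption. The sizes rest on the assumed predictor set, coefficients and correlations, fewer cross-validation repeats than planned, and no between-site shift.

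**What to change.** For the elastic-net models behind the calculator, use the test-site predictions already generated, in both directions:

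1. Report calibration intercept and slope with confidence intervals, and a calibration plot.
2. Report sensitivity, specificity and PPV with intervals at the chosen probability cut-off.
3. State that these count, together with AUC, towards the criterion for releasing the calculator.
4. Where they show miscalibration, recalibrate before release, for example by updating intercept and slope on the pooled cross-site predictions.

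Do not use a pass/fail calibration test, which 300 patients cannot support; report the intervals and let them carry the uncertainty.

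The cost is a few extra outputs and possibly a delayed or recalibrated release. No change is needed to the hypothesis tests, the sample size or the decision rules that output no probability.
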